### Study design

3.1

The study was designed in accordance with the Standard Protocol Items: Recommendations for Interventional Trials and Consolidated Standards of Reporting Trials 2010 guidelines^[7,8]^ (Additional File 1). The proposed study is a prospective, open-label, single-arm, and interventional clinical trial that will be conducted at the following 53 centers: Nagasaki University Hospital, Hokkaido University Hospital, Hokkaido Medical Center for Rheumatic Diseases, Katayama Orthopedic Rheumatology Clinic, University of Tsukuba Hospital, Saitama Medical University Hospital, Aoki Medical Clinic, Chiba University Hospital, Yokohama City University Medical Center, Yokohama City University Hospital, Yokohama Minami Kyousai Hospital, Yoshimi Hospital, Toyota Kosei Hospital, Chubu Rosai Hospital, Kyoto University Hospital, University Hospital Kyoto Prefectural University of Medicine, Osaka Medical and Pharmaceutical University Hospital, Osaka City University Hospital, National Hospital Organization Osaka Minami Medical Center, Kindai University Hospital, Kita-Harima Medical Center, Kobe University Hospital, Okayama University Hospital, Yamaguchi Prefectural Welfare Agricultural Cooperative Association Nagato General Hospital, Kagawa University Hospital, Ehime University Hospital, Kochi Medical School Hospital, Hospital of the University of Occupational and Environmental Health, Tobata General Hospital, PS Clinic, National Hospital Organization Ureshino Medical Center, National Hospital Organization Miyakonojo Medical Center, Miyazaki Zenjinkai Hospital, Chiyoda Hospital, Yoshitama Clinic for Rheumatic Diseases, Eiraku Clinic, Japanese Red Cross Nagasaki Genbaku Hospital, National Hospital Organization Nagasaki Medical Center, Sasebo Chuo Hospital, Sasebo City General Hospital, Fukushima Medical University Hospital, Toho University Ohashi Medical Center, Niigata Rheumatic Center, Nara Medical University Hospital, Tohoku Medical and Pharmaceutical University Wakabayashi Hospital, Aomori Prefectural Central Hospital, Nippon Medical School Hospital, Kurume University Medical Center, Seirei Hamamatsu General Hospital, Marunouchi Hospital, St. Marianna University Hospital, Japanese Red Cross Ogawa Hospital, and Shinonoi General Hospital.

In total, 155 RA patients will receive upadacitinib for a duration of 48 weeks. The study design is summarized in Figure 1.

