#### Intervention

3.3.3

Patients will receive upadacitinib at 15 mg/day and continue to receive the same dosage of MTX with or without a corticosteroid for 24 weeks (Stage I). If a EULAR-defined moderate response or a DAS28-CRP score of ≤3.2 is achieved at 12 weeks with a DAS28-CRP score of <2.6 at 24 weeks, MTX will be discontinued and upadacitinib with or without a corticosteroid will be continued until week 48 (Stage II). Patients not achieving a EULAR-defined moderate response and a DAS28-CRP score of ≤3.2 at 12 weeks or <2.6 at 24 weeks will be excluded from this study.

During the study period, the following treatments are prohibited: administration of a bDMARD or JAK inhibitor, other than upadacitinib; concomitant use of an immunosuppressant (i.e., azathioprine, cyclophosphamide, or cyclosporine), csDMARD, other than MTX, or an oral corticosteroid equivalent to >7.5 mg/day of prednisolone; intra-articular corticosteroid injections at the joints; and any nonsteroidal anti-inflammatory drug suppository. During the study period, the dosage of any oral nonsteroidal anti-inflammatory drug can be modified within the range approved in Japan.

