### Outcome measurements

3.4

Study visits will be conducted at baseline and 12, 24, 36, and 48 weeks after initiation of upadacitinib administration. The assessments are presented in Table 1. Clinical physicians will be blinded to joint assessments by MSUS.

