#### Secondary endpoints

3.5.2

The secondary endpoints of this study are as follows: (1) achievement of a DAS28-CRP score of ≤3.2 at weeks 12, 24, and 36; (2) achievement of a DAS28-CRP score of <2.6 at weeks 12, 24, 36, and 48; (3) clinical relapse (DAS28-CRP score of >3.2) at week 48 in patients who achieved a DAS28-CRP score of <2.6 at week 24; (4) achievement of an EULAR-defined moderate response at week 12; (5) changes in DAS28-ESR and DAS28-CRP scores from baseline to weeks 12, 24, 36, and 48; (6) changes in DAS28-ESR and DAS28-CRP scores from week 24 to 36 and 48; (7) changes in CDAI and SDAI values from baseline to weeks 12, 24, 36, and 48; (8) changes in CDAI and SDAI values from week 24 to 36 and 48; (9) achievement of a CDAI of ≤2.8 at weeks 12, 24, 36, and 48; (10) achievement of a SDAI of ≤3.3 at weeks 12, 24, 36, and 48; (11) changes in biomarker serum levels from baseline to weeks 12, 24, 36, and 48; (12) changes in biomarker serum levels from week 24 to 36 and 48; (13) changes in total PD and GS scores and combined PD score from baseline to weeks 12, 24, 36, and 48; (14) changes in total PD and GS scores and combined PD score from week 24 to 36 and 48; (15) change in vdH-mTSS from baseline to weeks 24 and 48; (16) change in vdH-mTSS from week 24 to 48; (17) change in the HAQ-DI data from baseline to weeks 12, 24, 36, and 48; and (18) change in the HAQ-DI data from week 24 to 36 and 48.

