### Sample size

3.8

First, the predicted point estimate and 95% confidence interval (CI) of the primary endpoint is 0.65 with a half-width of 10% of the 95% CI in the ORAL-Shift trial.^[17]^ Variability of the estimate, one-sided width 95% CI, is clinically valid. The sample size required at the start of upadacitinib monotherapy was calculated as 84. Next, in consideration that 60% of patients achieved a DAS28-CRP score < 2.6 with upadacitinib plus MTX combination therapy in the SELECT-COMPARE^[4]^ and SELECT-SUNRISE^[18]^ trials, the sample size necessary at the start of upadacitinib plus MTX combination therapy was calculated as 140. Here, the candidate predicted point estimates were calculated as 0.4 and 0.7 for the SELECT-COMPARE and SELECT-SUNRISE trials, respectively. The cohort of the SELECT-COMPARE trial was non-Japanese, while that of the SELECT-SUNRISE trial was Japanese. The majority, if not all, of the patients in the proposed cohort will be Japanese. The cohort of the proposed cohort is planned to be similar to that of the SELECT-SUNRISE trail. Because the cohorts will not likely be completely comparable, the effect was considered more conservatively than in the SELECT-SUNRISE trail, as the point estimate of the proposed study is 0.60. Finally, assuming that the dropout rate over the entire study period will be 10%, the target sample size was calculated as 155.

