### Statistical analysis

3.9

The primary analysis is planned to estimate the 95% CI of the primary endpoint (section 3.5.1) via Wilson's score interval.^[12]^ The primary endpoint will be evaluated from a set of participants who achieved a DAS28-CRP score of <2.6 during upadacitinib plus MTX combination therapy (Stage I). The primary analysis will control for type I errors at the 5% significance level. To support the clinical interpretation of the results of the primary analysis, participant-wise time courses of the DAS28-ESR and DAS28-CRP scores will be plotted. The distribution of changes in the total PD and GS scores and the combined PD scores will be summarized as histograms. Other statistical analyses are planned to explore the relationships between the measured results obtained as exploratory outcomes, as detailed in section 3.5.3. All other analyses will be considered as exploratory and will not be adjusted for multiplicity.

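### Change in DAS28, CDAI and SDAI after MTX is stopped is measured from the week-24 visit that selected the patients, so it carries an upward shift from regression to the mean

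*Protocol article*

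**What the plan says.** - Entry to Stage II (section 3.3.3) depends on a week-12 response condition together with a single week-24 score: "with a DAS28-CRP score of <2.6 at 24 weeks, MTX will be discontinued". Patients who miss the week-24 cutoff leave the study (sections 3.3.3 and 3.3.4), so only selected patients are followed to weeks 36 and 48.
- The secondary endpoints (section 3.5.2) include (6) "changes in DAS28-ESR and DAS28-CRP scores from week 24 to 36 and 48" and (8) "changes in CDAI and SDAI values from week 24 to 36 and 48".
- The visit plan (section 3.4) gives one week-24 visit: "Study visits will be conducted at baseline and 12, 24, 36, and 48 weeks after initiation of upadacitinib administration".
- The design (section 3.1) is a "prospective, open-label, single-arm, and interventional clinical trial", so no group continues MTX after week 24.
- Section 3.9 adds that "participant-wise time courses of the DAS28-ESR and DAS28-CRP scores will be plotted", as an aid to interpreting the primary result. It treats every analysis other than the primary one as exploratory and without multiplicity adjustment.

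**The concern.** A score that had to be low to count is low partly because of visit-to-visit variation. Its expected value at the next visit is therefore higher, even when nothing has changed in the patient. Here the selecting DAS28-CRP score is also the starting value for the change score. DAS28-ESR, CDAI and SDAI draw on joint counts and global assessments from the same visit, so they inherit part of the shift.

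The trial asks what happens once MTX is stopped, and endpoints (6) and (8) are the continuous measures of that. The artefact appears at exactly the moment MTX stops, and without a continuing-MTX group the raw change cannot separate the two. The plotted time courses show the same step. A reader could take a rise produced by the entry rule for a cost of stopping MTX.

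**Working it through.** **The plan's own figures (section 3.8).** The planning value "is 0.65 with a half-width of 10% of the 95% CI". At a proportion of 0.65 the Wilson 95% half-width first falls to 0.10 or below at n = 84 (0.09996). Then 84/0.60 = 140 and 140/0.90 = 155.6, against the stated 155. The chain reproduces to within rounding, so 84 patients and a 60% pass rate are sound inputs.

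**Inputs**
- Share passing the week-24 cutoff: 0.60, from "60% of patients achieved a DAS28-CRP score < 2.6 with upadacitinib plus MTX combination therapy". Section 3.8 also names 0.4 and 0.7 as candidates.
- Patients entering Stage II: 84 (section 3.8).
- SD of DAS28-CRP: 0.8 to 1.2. Assumed; not in the document.
- Correlation r between visits: 0.5 to 0.8, with 0.9 as a sensitivity value. Assumed; not in the document.
- Normal scores, stable true mean after week 24, no effect of stopping MTX.

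**Formula, week-24 cutoff only**

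Expected rise = (1 − r) × SD × φ(z) / share, with z = Φ⁻¹(0.60) = 0.253 and φ(0.253) = 0.386.

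0.386/0.60 = 0.644, so the expected rise is 0.644 × SD × (1 − r).

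| SD | r 0.5 | r 0.6 | r 0.7 | r 0.8 | r 0.9 |
|---|---|---|---|---|---|
| 0.8 | 0.258 | 0.206 | 0.155 | 0.103 | 0.052 |
| 1.0 | 0.322 | 0.258 | 0.193 | 0.129 | 0.064 |
| 1.2 | 0.386 | 0.309 | 0.232 | 0.155 | 0.077 |

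Simulation agrees with the closed form. For r 0.5 to 0.8 the range is 0.10 to 0.39. With 84 patients, the 95% CI for the mean change then lies wholly above zero in about 48% to 89% of trials, against a nominal 2.5%. Over the same SD and r, the range is about 0.15 to 0.58 if 40% pass and 0.08 to 0.30 if 70% pass.

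**Adding a week-12 gate.** Take one reading of the week-12 condition, DAS28-CRP ≤3.2, and assume a week-12 mean 0.3 points higher than at week 24. At SD 1.0 the rise falls to 0.27, 0.21, 0.15 and 0.10 for r 0.5, 0.6, 0.7 and 0.8. Over SD 0.8 to 1.2 it is about 0.08 to 0.32. The combined range, with or without this gate, is 0.08 to 0.39; at r = 0.9 it is 0.04 to 0.08.

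**Withdrawal at relapse.** Keeping only patients at or below 3.2 at weeks 36 and 48 (SD 1.0, no week-12 gate) leaves +0.05 to +0.17 for r 0.9 down to 0.5. The shift shrinks but stays positive.

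**Other indices.** An index correlated 0.8 with DAS28-CRP carries about 80% of the shift, in its own SD units.

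**Source of the shift.** Measured from a second week-24 reading independent of the selecting one, the simulated change is 0.00 for every r. The rise comes from using one reading twice.

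**Does a correction work?** The quantity (1 − r) × (mean of all patients assessed at week 24 − mean of those below 2.6) equals the artefact when there is no week-12 gate. With the gate, the r estimated from retained patients is restricted in range (a true 0.6 appears as about 0.47), and the correction misses the artefact by at most about 0.03 points.

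**The case against.** The strongest reply is that nothing is misused. Endpoints (6) and (8) are descriptive, no test or causal claim is attached to them, and section 3.9 calls them exploratory. That stands as a reason for low severity. It does not remove the bias, because the exploratory label deals with multiplicity and not with the choice of reference value.

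Second, the size rests on an SD and a correlation from outside the document, and the simplest calculation ignores the week-12 gate and withdrawal at relapse. Both points stand. They are why the range reaches down to 0.08, and lower still if r is near 0.9, and why the 48% to 89% figures are upper-end values for a simplified trial.

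Third, the statistical analysis plan is not shown and may already handle this. That is possible, so the article cannot be faulted for lacking a correction. What it does fix is that the selecting reading and the reference reading are the same.

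Two stronger readings are tempting and are not supported:
- **That the trial will, or must always, show worsening.** The bias is upward, but the observed change also reflects the true course. Continued improvement on upadacitinib after week 24 of a similar size could cancel it.
- **That the primary endpoint is biased in the same way.** It is a proportion staying at or below 3.2 and uses no change score. An excursion above 3.2 is a failure by definition, whatever caused it. Whether the planning value of 0.65 already includes such fluctuation cannot be seen from the document.

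**Conclusion.** The concern holds, as a minor point on secondary endpoints. Change from week 24 in endpoints (6) and (8) is biased upward by regression to the mean. With a stable true mean, no effect of stopping MTX, a 60% pass rate, SD 0.8 to 1.2 and r 0.5 to 0.8, the expected DAS28-CRP shift is about 0.08 to 0.39 points. DAS28-ESR, CDAI and SDAI are shifted less, because they are selected only indirectly. The direction of the bias follows from the design for any r below 1; its size depends on assumptions that the trial's own data can replace.

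**What to change.** In section 3.9, for endpoints (6) and (8):

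1. Report the observed change beside the rise expected from selection alone, (1 − r) × (mean week-24 score of all patients assessed at week 24 − mean of those with DAS28-CRP below 2.6). Estimate r from the week-12 and week-24 scores and give a bootstrap CI.
2. Label the correction approximate, because the week-12 gate restricts the range from which r is estimated (error up to about 0.03 DAS28-CRP points in simulation). For DAS28-ESR, CDAI and SDAI it also assumes that each index's link to the selecting score weakens between visits at the index's own r.
3. State that the raw change is not attributed to stopping MTX.

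Two descriptive rows are optional. One is the on-MTX change from week 12 to 24 in patients below 2.6 at week 12, noting that they are early responders and may still be improving. The other is the change from week 36 to 48, noting that withdrawal at relapse selects on week 36. If all patients at or above 3.2 at week 36 are withdrawn, a residual rise of up to about 0.12 points remains under no effect (week-12 gate applied).

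The cost is analysis wording and a few table rows, with no new visits or data. The downside is that the correction itself assumes a stable mean.

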#### Exploratory endpoints

3.5.3

For further research, the following exploratory endpoints will be assessed:

1.DAS28-ESR and DAS28-CRP scores at baseline and weeks 12, 24, 36, and 482.Patient pain visual analog scale score at baseline and weeks 12, 24, 36, and 483.Total PD and GS scores and combined PD score at baseline and weeks 12, 24, 36, and 484.VdH-mTSS at baseline and weeks 24 and 485.HAQ-DI at baseline and weeks 12, 24, 36, and 486.Biomarker serum levels at baseline and weeks 12, 24, 36, and 48

### AEs

3.6

All AEs that occur between the baseline visit and the end of week 48 will be recorded. If necessary, the investigators will administer appropriate treatments. A serious AE is defined as any adverse reaction resulting in any of the following outcomes: life-threatening condition or death; a condition that requires inpatient hospitalization or prolongation of existing hospitalization; and any condition threatening to cause disability or disability, congenital anomaly, or birth defect. All serious AEs will be documented in the medical records and reported to the CRB by the responsible investigator in accordance with Japanese regulations.

### Data collection and management

3.7

In this study, the data of each patient will be entered into an online, web-based electronic data-capture (EDC) system in the form of an electronic case report (e-CRF). The data of biomarkers, such as cytokines, reassessment MSUS results, and vdH-mTSS results will be collected as external data in electronic data format (e.g., Excel or comma-separated values), rather than entered into the EDC. According to the schedule presented in Table 1, the investigator will collect data at each patient visit during the study period. Appropriate and authorized persons (investigators, clinical trial physicians, and clinical trial collaborators) will be provided access to the EDC system in order to enter and modify the collected patient data. All data recorded in the e-CRF will be checked for consistency with the original materials.

All study findings and documents will be regarded as confidential. Patients will be identified on the e-CRF by an anonymous number, not by name. The confidentiality of all documents that identify the patient will be maintained by the investigator to ensure patient anonymity. During the study, a sponsor-investigator will perform regular site visits to review protocol compliance, conduct source data verification, assess drug accountability and management, and ensure that the study is being conducted according to pertinent regulatory and protocol requirements.

### Sample size

3.8

First, the predicted point estimate and 95% confidence interval (CI) of the primary endpoint is 0.65 with a half-width of 10% of the 95% CI in the ORAL-Shift trial.^[17]^ Variability of the estimate, one-sided width 95% CI, is clinically valid. The sample size required at the start of upadacitinib monotherapy was calculated as 84. Next, in consideration that 60% of patients achieved a DAS28-CRP score < 2.6 with upadacitinib plus MTX combination therapy in the SELECT-COMPARE^[4]^ and SELECT-SUNRISE^[18]^ trials, the sample size necessary at the start of upadacitinib plus MTX combination therapy was calculated as 140. Here, the candidate predicted point estimates were calculated as 0.4 and 0.7 for the SELECT-COMPARE and SELECT-SUNRISE trials, respectively. The cohort of the SELECT-COMPARE trial was non-Japanese, while that of the SELECT-SUNRISE trial was Japanese. The majority, if not all, of the patients in the proposed cohort will be Japanese. The cohort of the proposed cohort is planned to be similar to that of the SELECT-SUNRISE trail. Because the cohorts will not likely be completely comparable, the effect was considered more conservatively than in the SELECT-SUNRISE trail, as the point estimate of the proposed study is 0.60. Finally, assuming that the dropout rate over the entire study period will be 10%, the target sample size was calculated as 155.

### Statistical analysis

3.9

The primary analysis is planned to estimate the 95% CI of the primary endpoint (section 3.5.1) via Wilson's score interval.^[12]^ The primary endpoint will be evaluated from a set of participants who achieved a DAS28-CRP score of <2.6 during upadacitinib plus MTX combination therapy (Stage I). The primary analysis will control for type I errors at the 5% significance level. To support the clinical interpretation of the results of the primary analysis, participant-wise time courses of the DAS28-ESR and DAS28-CRP scores will be plotted. The distribution of changes in the total PD and GS scores and the combined PD scores will be summarized as histograms. Other statistical analyses are planned to explore the relationships between the measured results obtained as exploratory outcomes, as detailed in section 3.5.3. All other analyses will be considered as exploratory and will not be adjusted for multiplicity.

## Discussion

4

The main purpose of this clinical trial is to determine whether clinical relapse of RA can be avoided after discontinuation of MTX in patients who achieved clinical remission with upadacitinib plus MTX combination therapy.

The introduction of JAK inhibitors and bDMARDs has dramatically improved the management of a relatively large number of RA patients.^[3]^ In addition, several studies have evaluated changes in disease activity after discontinuation of MTX in RA patients who achieved a good response to MTX plus bDMARDs or JAK inhibitors.^[17,19–21]^ The ORAL-Shift trial showed that tofacitinib monotherapy after discontinuation of MTX was not inferior to continued tofacitinib plus MTX combination therapy, as determined by changes in the DAS28-ESR scores of RA patients who achieved low disease activity with tofacitinib plus MTX.^[17]^ However, no clinical study has yet evaluated disease activity using MSUS after discontinuation of MTX in RA patients who achieved clinical remission during treatment with MTX plus bDMARDs or JAK inhibitors.

Thus, the strength of this study is the prospective evaluation of treatment effects using MSUS, which can accurately and objectively assess disease activity at the joint level as well as the clinical disease activity indices. In addition, the serum levels of many biomarkers, including cytokines and chemokines, will be broadly analyzed, and parameters at baseline and 24 weeks will be assessed to predict non-relapse after discontinuation of MTX by integrating multilateral assessments (i.e., clinical disease activity indices, MSUS findings, and serum biomarkers).

We will be able to provide optimized treatment options if we could predict patients who could achieve clinical remission treated with upadacitinib plus MTX and then could discontinue MTX without a relapse, from the results of this study.
